**Moderating factors for uptake, use, and effects**			
	Age, sex, education level, internet use, and skills	Q1^a^ (baseline)	—
	Health literacy	Q1 (baseline): SBSQ-D^b^	—
	Attitude toward patient-doctor roles and patient involvement	Q1 (baseline)	Focus group discussions (baseline); interviews (2-6 months)
**Determining factors for uptake**			
	Expected usefulness; expected usability; concerns about privacy; perceived support from the general practitioner (GP)	Q1 (baseline)	Focus group discussions (baseline)
	Perceived health; presence of a chronic disease	Q1 (baseline)	—
**Use (reach, dosage, and fidelity)**			
	Personal health record (PHR) used to store data; PHR used to share data	Q2, Q3, and Q4^a^ (2, 3, and 6 months, respectively)	Interviews (2-6 months)
	Summary of general practice records (GP records) accessed	Log data: number of hit days during the study period (6 months); Q2, Q3, and Q4 (2, 3, and 6 months, respectively)	Interviews (2-6 months)
**Experiences with PHR and access to the summary of GP records**			
	Experienced barriers and facilitators; experienced usability; experienced usefulness, benefits, and drawbacks	Q2, Q3, and Q4 (2, 3, and 6 months, respectively)	Think-aloud observations (1-3 months); interviews (2-6 months)
**Primary outcomes: changes in the following**			
	Active role in decision making	Q1, Q4: PIH^c^ (baseline, 6 months)	Interviews (2-6 months)
	Active role in care delivery	Q1, Q4: PIH (baseline, 6 months)	Interviews (2-6 months)
	Medication adherence	Q1, Q4: MARS-5^d^ (baseline, 6 months)	Interviews (2-6 months)
**Secondary outcomes: changes in the following**			
	Knowledge about the disease and treatment	Q1, Q4: PIH (baseline, 6 months)	Interviews (2-6 months)
	Confidence in communication with the GP	Q1, Q4: PEPPI-5^e^ (baseline, 6 months)	Interviews (2-6 months)
	Satisfaction with GP care	Q1, Q4 (baseline, 6 months)	Interviews (2-6 months)
	Patient-GP relationship	Q4 (6 months)	Interviews (2-6 months)
	Use of GP services	Q1, Q4 (baseline, 6 months)	Interviews (2-6 months)

^a^Q1, Q2, Q3, and Q4: questionnaires 1, 2, 3, and 4, respectively.

^b^SBSQ-D: Dutch version of the Set of Brief Screening Questions.

^c^PIH: Partner in Health scale.

^d^MARS-5: Medication Adherence Report Scale.

^e^PEPPI-5: Perceived Efficacy in Patient-Doctor Interactions scale.

Q2 and Q3 are brief, containing 6 self-generated questions to check whether participants are able to navigate through the PHR, medication list, problem list, and consultation notes and are able to comment on the completeness and usefulness of the information. These questions are formulated as statements to which participants can express their agreement on a 5-point Likert scale. In addition, 2 open questions will be added asking how patients feel about using the PHR and about accessing the summary of their GP records.

Q4 is similar to Q1; it includes the same validated scales to assess for intermediate effects, allowing us to assess differences over time. It also contains self-generated items on the usability of the system and on usefulness of the PHR and information on the summary of the GP record and use of GP services, which are formulated as statements with a 5-point Likert scale to express patients’ agreement or disagreement.

#### Log Data and Page Views

Log data on the number of days during the 6-month study period when the patients log in to the system (hit days in 6 months) and view their medication list, problem list, test results, and consultation notes will be collected to assess the actual utilization of the PHR to access the summary of GP records.

#### Routine Patient Data From General Practices

To describe our sample of study participants in relation to the population that the sample was obtained from, we will collect routine data (age, sex, prevalence of chronic disease, and frequency and number of contacts with the GP or practice nurse) from GP practices for the groups of patients from which we have obtained our samples.

#### Focus Group Discussions

Before the implementation of the intervention, we will conduct a focus group discussion with each of the 3 patient groups who participate in the study, for example, one with polypharmacy patients, one with parents of young children, and one with other adult patients. The sessions will start with a brief explanation about PHRs in general and MijnZorgnet specifically using a short movie. Subsequently, we will show the PHR and the pages that the patients will be able to view in their medical records in general practice. We will provide enough time for answering questions about the PHR and access to medical records and the National Connection Point. We will use a predefined topic list based on our conceptual framework to guide the discussion, including expectations about the usefulness of keeping a PHR and viewing the professional summary of the GP records and ideas about patient involvement in care and concerns about privacy and security. Two investigators will moderate the sessions, which will be audiotaped.

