The PHR and Web-based access to the summary of the GP records will be introduced to patients in a brochure that they will receive together with the invitation to participate in the study, signed by their GPs. When they log in to the PHR for the first time, they will be guided through an instruction on how to use the PHR. In addition, the participants can contact the MijnZorgnet help desk about questions regarding the PHR and how to access their summary record. The GP staff can be approached for questions about the content of the summary record.

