The participants of the qualitative study strand among patients will be obtained from the sample of participants of the quantitative study strand who indicate in the first questionnaire to be willing to participate in the qualitative study. To obtain a sample of patients who vary in age, gender, and education level, we will use purposive sampling. The sample size of the qualitative study strand among patients will be determined using the saturation principle. For the focus group study, we expect to achieve saturation across groups by conducting 3 focus group discussions (one for polypharmacy patients, one for parents of young children, and one for the other patients), with each group including 5-8 participants. In addition, we strive to achieve saturation within groups by inviting patients who differ in age, gender, and education level. If we feel that saturation has not been reached, we will consider conducting more focus group discussions. We will continue with think-aloud observations and semistructured interviews until we detect no new information in 3 consecutive observations or interviews.

For the study strand at GP staff level, we aim to include not only GPs but also practice nurses and practice assistants as participants to obtain a complete understanding of the use and effects of the PHR and to gain access to the summary of the GP records. Practice nurses and practice assistants also enter information in the GP records, and they may also be approached by patients with questions regarding the content of the records. Because their roles differ from those of the GP, their attitudes, experiences, and opinions concerning the PHR and access to the records may also differ, and therefore, their inclusion in the study may be useful. Sampling for the focus group study among GP staff will be performed purposively. To achieve saturation within focus groups, we will include at least two GPs, a practice nurse, a practice assistant, and a GP in training in each group. To achieve saturation across groups, we will conduct a focus group discussion with the GP staff in each of the 3 practices. All GPs, practice nurses, practice assistants, and GPs in training will participate in the Q-study at the end of the study period.

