#### Semistructured Interviews

We will conduct semistructured interviews to explore patients’ experiences, opinions, and concerns regarding the PHR and access to the summary of the GP records. A topic list has been established based on our conceptual framework, including barriers and facilitators for using the PHR and access to the summary GP record, usability and usefulness of the PHR to store and share information, experienced usefulness (understandability, credibility, and desirability) of the information in the GP records, experienced benefits and drawbacks related to the use of the PHR and accessing the summary GP record, experienced changes in relation with the GP, involvement in decision making and disease management, and patient-centeredness of care. The interviews will be conducted over a period of 5 months, which allows us to obtain information from more and less experienced patients. The interviews will be audiotaped.

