### Strengths and Limitations

Our protocol has some strengths and limitations. We consider the use of a clear conceptual framework as a strength of the study, even though drawing on two theories (the Unified Theory of Acceptance and Use of Technology and Snyder’s model on patient involvement), it is a rather complex framework [1,25]. This framework has helped us include all variables that are likely to be relevant to our study, and it will also guide the interpretation of findings. The mixed-methods design enables us to assess the uptake and potential effects and obtain a deeper understanding of the use and nonuse of the intervention and the effects or absence of the effects [32]. Another strength is that we will conduct the study at two levels, patient level and GP staff level. GP staff is likely to influence the use and impact of the intervention among patients. Because the relationship between patients and GP staff may change due to the intervention, it is important to obtain information from both patients and GP staff. Another strong point of this study is the use of validated instruments to assess the effects of the intervention. However, these instruments have not been validated among parents of young children. Therefore, we will need to interpret the results based on the questionnaires on the effects on involvement-related outcomes in parents with great care. Multiple testing may be another limitation of our study. We will deal with this in the interpretation of our results by focusing on the primary outcomes and aligning qualitative findings with the results of the comparisons. We will conduct this study in the practices of GPs who are open to innovation and willing to provide their patients access to their records. We are aware that this setting is not representative of Dutch general practice. In addition, we are aware that our findings about adoption will need to be interpreted with caution because our participants, particularly those who take part in the focus group discussions, think-aloud observations, or semistructured interviews, will receive more information about the PHR and its use, than is likely to occur in a real-life setting. Furthermore, we realize that not including patients older than 75 years may also influence our findings. Obviously, we will take this into account during the interpretation of our results.

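### Focus group, think-aloud and interview participants get extra exposure to the PHR but have no separate handling in the described analyses, and the stated caveat covers adoption only

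*Protocol article*

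**What the plan says.** The support offered to every participant is set out in the section on the MijnZorgnet intervention: a brochure with the invitation, a help desk, GP staff for questions on content, and a first log-in guide ("When they log in to the PHR for the first time, they will be guided through an instruction on how to use the PHR").

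Patient focus group members get more than this before launch. According to Focus Group Discussions (patient level), "The sessions will start with a brief explanation about PHRs in general and MijnZorgnet specifically using a short movie". Then: "Subsequently, we will show the PHR and the pages that the patients will be able to view in their medical records in general practice". And: "We will provide enough time for answering questions about the PHR and access to medical records and the National Connection Point". The topic list also covers ideas about patient involvement in care.

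Two later strands add contact. Table 1 places think-aloud sessions at 1-3 months; they include people opening their record through the PHR for the first time. It places interviews at 2-6 months, on topics that include "involvement in decision making and disease management, and patient-centeredness of care".

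These people are not a separate sample. Setting, Study Population, and Sample Size states: "The participants of the qualitative study strand among patients will be obtained from the sample of participants of the quantitative study strand". They volunteer in the first questionnaire and are then chosen to vary in age, gender and education.

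Adoption, a primary outcome, is defined as at least one use of the PHR to access the summary record. The quantitative analysis section regresses adoption on patient characteristics and compares changes in involvement between users and nonusers by t test in each patient group. It mentions no exclusion, flag or term for qualitative-strand participants.

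Strengths and Limitations concedes that participants, especially those in the three qualitative strands, "will receive more information about the PHR and its use, than is likely to occur in a real-life setting". It draws the consequence for adoption findings only, and the remedy is caution in interpretation.

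**The concern.** The extra exposure is a research procedure, not part of the intervention, and it bears on the outcomes being measured.

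- **Adoption.** The threshold is a single access, so one demonstration could plausibly tip a participant over it. The conceptual framework itself names perceived usefulness and usability as determinants of uptake, and the session addresses both. A first access made during a think-aloud session would also meet the definition, and the article does not separate it from access that a patient makes unprompted.
- **Involvement outcomes.** Focus groups and interviews discuss involvement in care, which is close to what the six-month questionnaire (Q4) measures. If the people with this contact end up mainly among the users, part of a user-nonuser difference could come from the contact and not from access to the record.

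The authors saw the first issue. A verbal caveat, however, gives the reader no means of judging how much caution is needed, and the second issue has no caveat.

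**Working it through.** **Inputs** (Setting, Study Population, and Sample Size): 550 sampled per patient group; participation 25%-50%; uptake about 10%; 50 users and 100 nonusers expected per group; focus groups of 5-8, one per patient group.

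**The plan's own figure.** 10% of 500 = 50 users. The figure of 500 per group stands in the Abstract and is plausible as what is left of 550 after GP exclusions (an assumption); 10% of 550 = 55. So the planned 50 follows if uptake applies to everyone invited. If it applies only to responders, 550 × 25%-50% = 137.5-275 responders and 10% of them is about 14-28 users.

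**Attendees as a share of users, planned base (50 users, 100 nonusers)**

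| Attendees who adopt | Share of users | Share of nonusers |
|---|---|---|
| Same rate as others (50/150) | 3.3%-5.3% | 3.3%-5.3% |
| Half | 2.5/50 = 5% to 4/50 = 8% | 2.5/100 = 2.5% to 4/100 = 4% |
| All (extreme) | 5/50 = 10% to 8/50 = 16% | 0% |

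**The same share on the responder base**, with 10% uptake among the non-attendees:

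- All adopt: 5/(5 + 0.1 × 270) = 5/32 = 16%, to 8/(8 + 0.1 × 129.5) = 8/20.95 = 38%.
- Half adopt: 2.5/(2.5 + 27) = 8%, to 4/(4 + 12.95) = 24%.
- All at 10%: equal shares in both arms, 5/275 = 2% to 8/137.5 = 6%.

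**Shift in measured uptake.** If all attendees adopt instead of 10% of them, uptake rises by 0.9 × attendees / denominator:

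- denominator 550: 4.5/550 = 0.8 to 7.2/550 = 1.3 percentage points;
- denominator 275: 1.6 to 2.6 points;
- denominator 137.5: 3.3 to 5.2 points.

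These compare with an assumed uptake of about 10%.

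**Bias in the user-nonuser comparison.** Bias = (share among users − share among nonusers) × d, where d is the effect of attendance on the change score in SD units. The article gives no effect size or SD, so d is an assumption. On the planned base:

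| d (assumed) | Same rate | Half adopt | All adopt |
|---|---|---|---|
| 0.3 | 0 | 0.007-0.012 | 0.03-0.05 |
| 0.5 | 0 | 0.013-0.02 | 0.05-0.08 |
| 0.8 | 0 | 0.02-0.03 | 0.08-0.13 |

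For scale, the difference detectable with 80% power is (1.96 + 0.84) × √(1/50 + 1/100) = 0.49 SD. A bias of 0.05 SD would move the two-sided 5% type I error to about 6.0%, 0.08 SD to about 7.5%, and 0.128 SD to about 11.5%.

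On the responder base with all attendees adopting and d = 0.5, the bias is 0.5 × 5/32 = 0.08 to 0.5 × 8/20.95 = 0.19 SD.

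All these figures cover focus groups only. Think-aloud and interview numbers are set by saturation, so their contribution cannot be calculated.

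**The case against.** The strongest objection concerns a reading that a reader might infer: that the extra exposure is concentrated among the users. The article does not support it. Focus groups take place before the intervention is implemented, when nobody is yet a user or nonuser. Members are selected for variety in age, gender and education, not for intention to use. No user-nonuser split is given, and at equal adoption the bias is zero. This stands, so over-representation among users is a possibility to be checked and not a finding.

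A related temptation is to quote 38% as the likely share. That needs the smallest response, the largest focus group, uptake counted among responders only, and adoption by every attendee. On the plan's own 50 users the ceiling is 16%.

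It can also be said that the authors already disclose the problem, that a fuller protocol or analysis plan may contain a sensitivity analysis, that the study is exploratory, and that self-selection into use is a much larger threat than 5-8 people per group. All of this is fair and limits the weight of the point. It does not remove it: the handling that is stated is interpretive only and stops at adoption.

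Purposive sampling for variety should spread attendees across age, gender and education, so distortion of the predictor estimates is not shown either. The later strands differ somewhat. Everyone in a think-aloud session opens the record, and interviews ask about experiences of use, so these strands probably lean toward users. Nonusers may nevertheless be interviewed about barriers.

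**Conclusion.** The point holds in a limited form. Participants in the qualitative strands receive exposure that the intervention does not include, they belong to the survey sample, the described analyses do not treat them separately, and the acknowledgement covers adoption but not the involvement outcomes.

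At the planned 50 users per group the possible effect of the focus groups is modest: at most 10%-16% of users, and about 0.05-0.08 SD of bias if every attendee adopts and attendance shifts change scores by an assumed 0.5 SD. It becomes material only if users are far fewer than planned and nearly all attendees adopt. It is nil for the user-nonuser comparison if attendees adopt like everyone else. For uptake, the extreme case adds 0.8-1.3 points with all 550 sampled as the denominator, or 1.6-5.2 points among responders. Adoption shares and d are assumptions throughout; the article supplies neither.

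**What to change.** 1. Flag every participant who attended a focus group, a think-aloud session, or an interview held before Q4.
2. Report uptake and its predictors with and without focus group attendees.
3. Do not count a first access made during a think-aloud session as spontaneous adoption; report such cases separately.
4. Repeat the user-nonuser comparison of the involvement outcomes without flagged participants, as a sensitivity analysis beside the full one.
5. Extend the caveat in Strengths and Limitations to the involvement outcomes.

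The cost is one flag variable and a repeated analysis, which remains feasible although the Results section reports that analysis is underway. Leaving out focus group attendees removes 5-8 people per group, about 3%-5% of the planned 150, so intervals widen slightly. Leaving out all flagged participants removes more, and dropping interviewees removes mainly users. The restricted comparison should therefore stand next to the full one and not replace it.

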#### Think-Aloud Observation and Introspection

We will use the think-aloud method to assess the usability and usefulness of the MijnZorgnet PHR and avoid reporting bias [61-64]. We will ask patients to verbalize their thoughts while they perform predefined tasks, such as checking their medication list in their GP records. We will complement the think-aloud method with introspection [63], asking participants to explain why they performed tasks the way they did. To assess the extent to which information in the GP record is clear, understandable, desirable, and valuable to them, we will ask participants to comment on the information that they view in their GP records [65]. The think-aloud sessions will be conducted with patients who access their GP records for the first time through the PHR, and those who have logged in before. We will explain the method to them at the start of the session. Think-aloud observations and interviews will be audiotaped.

#### Semistructured Interviews

We will conduct semistructured interviews to explore patients’ experiences, opinions, and concerns regarding the PHR and access to the summary of the GP records. A topic list has been established based on our conceptual framework, including barriers and facilitators for using the PHR and access to the summary GP record, usability and usefulness of the PHR to store and share information, experienced usefulness (understandability, credibility, and desirability) of the information in the GP records, experienced benefits and drawbacks related to the use of the PHR and accessing the summary GP record, experienced changes in relation with the GP, involvement in decision making and disease management, and patient-centeredness of care. The interviews will be conducted over a period of 5 months, which allows us to obtain information from more and less experienced patients. The interviews will be audiotaped.

### Collection of Data at the General Practice Staff Level

#### Focus Group Discussions

We will conduct a focus group discussion with GPs, practice nurses, and practice assistants in each of the 3 centers for general practice before the implementation of the intervention. The topic list for these focus group discussions contains the perceptions of the GP staff about introducing a PHR and access to the summary of GP records regarding reporting habits, work load, relationship with patients, and ideas and concerns about confidentiality. The focus group discussions will be moderated by two researchers. The sessions will be audiotaped.

#### Ranking of Statements Using Q-Methodology

At the end of the study period, we will explore the opinions and concerns of the GP staff about the usefulness, benefits, and drawbacks of patient access to the professional summary of their record through the standalone PHR using Q-methodology [66-68]. Q-methodology is primarily a qualitative research method. However, it is a combination of quantitative and qualitative techniques used to identify shared opinions. Similar to other qualitative research methods, purposive sampling is used to obtain a sample of participants with variations in potentially relevant characteristics, for example, age or profession. Participants of a Q-study rank a set of statements on a response grid according to the extent they agree (+1 to +5), feel neutral (0), or disagree with each statement (−1 to −5). Using factor analysis (quantitative technique), the patterns of opinions among participants who share characteristics may be revealed [66,67]. We will formulate statements based on findings from the focus group discussions, think-aloud interviews, semistructured interviews, questionnaires, and literature.

